## Abstract

**Background:**

Depression in primary care is common, yet this costly and disabling condition remains underdiagnosed and undertreated. Persisting gaps in the primary care of depression are due in part to patients’ reluctance to bring depressive symptoms to the attention of their primary care clinician and, when depression is diagnosed, to accept initial treatment for the condition. Both targeted and tailored communication strategies offer promise for fomenting discussion and reducing barriers to appropriate initial treatment of depression.

**Methods/design:**

The Activating Messages to Enhance Primary Care Practice (AMEP2) Study is a stratified randomized controlled trial comparing two computerized multimedia patient interventions --- one targeted (to patient gender and income level) and one tailored (to level of depressive symptoms, visit agenda, treatment preferences, depression causal attributions, communication self-efficacy and stigma)--- and an attention control. AMEP2 consists of two linked sub-studies, one focusing on patients with significant depressive symptoms (Patient Health Questionnaire-9 [PHQ-9] scores ≥ 5), the other on patients with few or no depressive symptoms (PHQ-9 < 5). The first sub-study examined effectiveness of the interventions; key outcomes included delivery of components of initial depression care (antidepressant prescription or mental health referral). The second sub-study tracked potential hazards (clinical distraction and overtreatment). A telephone interview screening procedure assessed patients for eligibility and oversampled patients with significant depressive symptoms. Sampled, consenting patients used computers to answer survey questions, be randomized, and view assigned interventions just before scheduled primary care office visits. Patient surveys were also collected immediately post-visit and 12 weeks later. Physicians completed brief reporting forms after each patient’s index visit. Additional data were obtained from medical record abstraction and visit audio recordings. Of 6,191 patients assessed, 867 were randomized and included in analysis, with 559 in the first sub-study and 308 in the second.

**Discussion:**

Based on formative research, we developed two novel multimedia programs for encouraging patients to discuss depressive symptoms with their primary care clinicians. Our computer-based enrollment and randomization procedures ensured that randomization was fully concealed and data missingness minimized. Analyses will focus on the interventions’ potential benefits among depressed persons, and the potential hazards among the non-depressed.

**Trial registration:**

ClinicialTrials.gov Identifier: http://NCT01144104

## Background

Depressed patients experience impairment in multiple domains of functioning and well-being [1-7], poorer medical outcomes from chronic conditions [8,9], and increased health care costs [10-12]. Despite improvements in physician training and in systems integrating mental health and primary care, depression remains underdiagnosed in the primary care setting [13-16], the *de facto* mental health treatment system for adults [17-20]. Mild depression is more likely to be overlooked, but a study of undetected cases found that 53% met criteria for major depression one year later [21]. Even when diagnosed promptly, depression is often under-treated [22-25]. These gaps in care may partly be due to patients being reluctant to bring depressive symptoms promptly to the attention of primary care clinicians and to accept initial treatment for depression when it is offered.

Stigma associated with depression is a major barrier to effective diagnosis and treatment in primary care. Silence in the face of depression can be an effective way of avoiding stigmatization and its consequences, including social rejection, overt discrimination, and personal shame [26-29]. Some groups, such as African-Americans, Latinos, and men, are less likely than others to seek care for depression, due in part to such factors as greater perceived stigma and poorer access to high quality health care [25,30-40].

To address these primary care barriers to patient discussion of and initial acceptance of treatment for depression, we developed two alternative communication interventions designed for use by primary care practices [41-44]. The first intervention was a brief, targeted public service announcement (PSA) modeled after direct-to-consumer advertisements for antidepressant drugs but free of commercial bias. The second was a longer, theory-driven, tailored interactive multimedia computer program (IMCP). The overarching objective of this study was to compare the effects of these interventions and an attention control intervention on depression-related behaviors, care processes, and outcomes.

## Methods/design

### Overview of RCT design

The Activating Messages for Enhancing Primary Care Practice (AMEP2) Study was designed as a multicenter, stratified, parallel-group randomized controlled trial comparing three arms: a targeted patient intervention, a tailored patient intervention, and an attention control. Consenting patients were randomly assigned to and viewed an intervention just before a scheduled primary care office visit during which they also completed a previsit survey that included items used for tailoring/targeting, Patients also completed surveys immediately after this *index visit* and at 12-weeks follow-up. Physicians completed brief reporting forms after each patient visit. Additional data were obtained from medical record abstraction and (in a subsample) visit audio recordings.

We conceptualized the trial as two linked sub-studies, one focusing on patients with significant depressive symptoms (Patient Health Questionnaire-9 [PHQ-9] scores ≥ 5) [45], the other on patients with few or no depressive symptoms (PHQ-9 scores < 5). As described below, Sub-study 1 focuses on intervention effectiveness, Sub-study 2 on potential hazards (clinical distraction and overtreatment).

### Description of interventions

In the developmental phase of the project [41-44], we produced two new experimental interventions for improving the detection and treatment of depression in the primary care setting. Each intervention was grounded in a particular approach to creating educational experiences that are relevant to groups and individuals.

The public service announcement (PSA) intervention used *targeted* health messages. Targeted health messages involve segmenting a general population into smaller, more homogeneous units [46]. Typical segments are based on one or more readily observable factors such as age, sex, race or ethnicity, income level, occupation, area of residence, or medical history. Effective targeting, commonly used in social marketing campaigns, uses formative research, such as focus groups, to segment audiences and devise targeted persuasion strategies that are pre-tested for impact. Effectiveness is greatest when the messages emphasize the positive, short-term benefits of change and personal relevance to the listener [47]. Effectiveness is enhanced further when the campaign uses positive role models (such as individuals treated successfully for depression) to enhance social learning and reinforces messages with direct interpersonal influence from credible peers or leaders. The PSAs used in this RCT were targeted to patient gender and income level and were designed to encourage patients to seek depression care and request information (such as whether depression could constitute a reasonable explanation for the presenting symptoms) or diagnostic or therapeutic action (such as prescribing an antidepressant or referring to a mental health professional [48]).

The interactive multimedia computer program (IMCP) used *tailored* health messages. Such methods use information elicited from the respondent, often through a computerized interface, in crafting messages specific to that respondent [49]. In this way, the process of tailoring essentially segments a target audience even further, to the individual level. A growing body of evidence suggests that interventions that are personally tailored to individual mediators or modifiers of health behavior are superior to non-tailored interventions in improving various health behaviors and outcomes across a broad array of patient populations and target conditions [50-55], including depression in primary care [56]. Studies have shown that tailored health messages are better remembered, read, and perceived as relevant [57]. The IMCP provided descriptive and evaluative feedback tailored to the patient based on the following constructs from the previsit survey: level of depressive symptoms [45]; visit agenda (intention to request treatment vs. intention only to discuss depression vs. no intention to discuss depression); treatment preferences; depression causal attributions; communication self-efficacy and depression-related stigma.

Tailored and targeted messages increase the chances of engaging audiences with relevant messages, of creating stronger intentions in recipients to engage in behavior change, and of producing faster and longer-lasting behavioral results. In particular, they can enhance self-efficacy, or the perceived ability to complete a specific task, such as seeking medical care for depression. Perceived barriers to change and the readiness to change can be addressed by reminding recipients of their success in changing their own behavior and by sharing with them the experiences of their normative group.

Individuals randomized to the control intervention viewed a 2.9-minute publicly available educational video on insomnia with a focus on sleep hygiene. This video was chosen as the control because it was comparable in length and format to the experimental PSA and focused on sleep problems that are commonly seen among both depressed and non-depressed patients in primary care.

### Outcome measures for depressed and Non-depressed Sub-studies

AMEP2 consists of two linked sub-studies with the samples drawn from a study population partitioned by the level of depressive symptoms.

### Sub-study 1: patients *with* clinically significant depressive symptoms

This sub-study involves a sample of approximately 500 patients with a Patient Health Questionnaire-9 (PHQ-9) score of ≥ 5 (mild or greater depressive symptoms) on the previsit survey.

**Key Outcome: Initial Depression Care** The key process of care measure is a composite outcome termed *Components of Initial Depression Care (CIDC).* CIDC is coded positive if an antidepressant prescription or mental health referral is provided at the index study visit among the subset of participants with a high likelihood of clinically significant depression (defined as a baseline PHQ-9 score ≥ 10). This outcome is defined as “key” based on the primary study goal, which is to increase patient engagement in care at the initial visit. For patients with clinically significant depression, evidence supports the use of antidepressants and/or psychotherapy or counseling [58-60], and the study was powered to detect a significant intervention effect on this outcome. It is hypothesized that the active interventions will result in a greater likelihood that physicians will offer and patients will accept these treatments.

**Other outcomes** Other outcomes pertinent to Sub-study 1 include effects of the two active interventions on primary care follow-up interval; self-reported physical and mental health at 12 weeks; patient engagement with care during and immediately after the index visit and patient self-efficacy for communication immediately after the index visit; depression-related stigma immediately after the index visit and at 12 weeks; and suicide inquiry by the physician during the index visit.

(1) *Effect of the intervention on primary care follow-up interval.* Based on consensus of the study investigators and advisors, we define a minimally acceptable return visit interval for those not offered antidepressants or a mental health referral as within 2 weeks for those with a PHQ-9 score >14 (consistent with at least moderate depression) and within 4 weeks for those with a PHQ-9 score in the interval from 5 to 14. The former group is dominated by patients with clinically significant depression of more than moderate severity but may include some “false positives”; the latter group consists of a diverse mix of patients including many with dysthymia and sub-syndromal depression [61]. Therefore, in many circumstances, timely followup and careful re-evaluation, rather than immediate antidepressant therapy or referral, may represent good care. Because of the scant evidence base and difficulty in determining the reason for the follow-up interval, this outcome was not included as part of CIDC (the key outcome identified above). It is hypothesized that the active interventions will result in greater adherence to the acceptable follow-up intervals.

(2) *Effects of the interventions on depression severity and self-reported health at 12 weeks follow-up*. These outcomes (using the PHQ-8 [61,62] for depressive symptoms and the SF-12 [63] for self-reported physical and mental health) are based on telephone surveys of patients. It is hypothesized that the active interventions will result in greater improvement in patient functional status at 12 weeks.

(3) *Effects of the interventions on patient self-efficacy for communication with the physician and on engagement with care.* Self-efficacy for communication with the physician is assessed using a 6-item scale modified from the perceived efficacy in patient-physician interactions (PEPPI) scale of Maly et al [64]. The modifications were to modify the wording of the 5-item version of the PEPPI scale to be specific to “mental health concerns” and to add an additional item, worded “*How confident are you that you could talk about depression with a doctor if you wanted to?”* Engagement with care is assessed based on patient-reported readiness for discussion of depression, actual discussions of depression, and requests for information about and treatment for depression. It is hypothesized that the active interventions will result in greater patient communication self-efficacy and engagement.

(4) *Effects of the interventions on depression-related stigma*. We assess this outcome using a 5-item scale modified from Kantor’s Depression Self-Stigma Scale [65]. The underlying hypothesis is that depression-related, patient-centered education and support as delivered by the PSA and IMCP will reduce depression-related stigma.

(5) *Suicide inquiry.* Our prior research suggests that for patients with significant evidence of depression, there is a reluctance by physicians and their patients to discuss self-harm and suicide ideation [66]. By reducing the patient barrier to discussing depression, it is hypothesized that the active interventions will result in increased suicide inquiry by the physician.

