**Sub-study 1: patients*****with*****clinically significant depressive symptoms (baseline PHQ-9 ≥ 5)**			
Process of care			
Key outcome - components of initial depression care (CIDC): antidepressant prescription and/or mental health referral among participants with baseline PHQ-9 ≥ 10*	X		PQ, PCPQ, MRR
Others			
Antidepressant prescription and/or mental health referral among all sub-study participants*	X		
Follow-up with PCP at an appropriate interval†	X		
Inquiry regarding self-harm/suicidal thoughts	X		
Patient function			
PHQ-8^‡^ score	X	X	PQ
SF-12 Mental Component Summary score		X	
SF-12 Physical Component Summary score		X	
Patient engagement in depression care			
Readiness			PQ
To discuss depression (in general) with PCP	X		
To discuss depression treatment with PCP	X		
Self-efficacy			
For recognizing depression	X	X	
For discussing depression with PCP	X	X	
Provider-patient interaction			PQ, PCPQ, MRR
Discussion of depression	X		
Patient request for depression treatment	X		
Patient perceived depression stigma	X	X	PQ

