### Power calculations and sample size

By setting target sample sizes of 170 subjects per arm, the effectiveness sub-study was designed to provide 80% power to detect between-arm (pairwise) differences in the proportion receiving CIDC of 15 percentage points and standardized differences of 0.3 standard deviations (sd) in the mean levels of continuous outcomes, under two-sided testing with alpha = 5% [71]. For the sub-study focusing on non-depressed patients, the target enrollment of 102 subjects per arm provides 80% power to reject the noninferiority null hypothesis that exposure to an experimental intervention groups (N = 204 in the PSA/IMCP groups) is associated with at least a 3.5 percentage point increase in the extremely low risk anticipated for antidepressant prescribing in the control group (N = 102), under one-sided testing with alpha = 5% and assuming that the true risk is 1% in each of the three groups [72]. For pairwise comparisons of means, a sample size of 102 in each arm of the non-depressed sub-study provides greater than 80% power to detect differences of 0.4 sd [71].

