### Planned analytic approach

For all outcomes except for antidepressant behavior in the non-depressed patients, analyses will be implemented using multiple regression models for clustered data to account for the nesting of patient-level observations within providers and, for longitudinally assessed outcomes, the nesting of repeated measures within patients. Most analyses will take the form of generalized linear mixed models [73], with logistic regression models estimated via generalized estimating equations [74] used as a robust backup in case mixed-model assumptions are violated or computational difficulties (lack of convergence) are encountered.

In generalized linear mixed models, random effects will be specified for the physician (to account for the nesting of patients within physician). For longitudinal outcomes, random effects will also be specified for patient. The key independent variable will be the study group assignment (control vs. PSA vs. IMCP) and additional independent variables will be included to account for the stratified study design. Wald tests, point estimates and 95% Confidence Intervals will be used to assess hypothesized contrasts among the study arms.

Because the incidence of antidepressant behavior in the non-depressed patients is expected to be very low and the primary contrast of interest is for testing the one-sided noninferiority hypothesis that the incidence is not 3.5 percentage points higher in the combined PSA/IMCP groups versus the control, we will use restricted maximum likelihood methods to construct a 2-sided 90% confidence interval for the PSA/IMCP vs. Control risk difference in antidepressant prescribing risk to assess this null hypothesis, as described by Farrington and Manning [72].

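### The follow-up-interval outcome is defined only for patients not offered treatment, a status set after randomisation that the interventions are meant to change

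*Protocol article*

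**What the plan says.** Under Sub-study 1, other outcomes, item (1), the protocol article sets the standard: "we define a minimally acceptable return visit interval for those not offered antidepressants or a mental health referral". The limit is 2 weeks for PHQ-9 above 14 and 4 weeks for PHQ-9 5 to 14. The item ends with a between-arm hypothesis: "It is hypothesized that the active interventions will result in greater adherence to the acceptable follow-up intervals". It also keeps follow-up apart from treatment: "this outcome was not included as part of CIDC (the key outcome identified above").

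For the key outcome in the same section, the expectation is: "It is hypothesized that the active interventions will result in a greater likelihood that physicians will offer and patients will accept these treatments".

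Table 1 lists "Follow-up with PCP at an appropriate interval" as a Sub-study 1 process outcome. It names no denominator and gives no rule for patients who were offered treatment. Under Planned analytic approach, the models regress outcomes on arm: "The key independent variable will be the study group assignment (control vs. PSA vs. IMCP"). Covariates for the stratified design are added.

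**The concern.** Patients are randomised and view their assigned material before the visit. Whether treatment is offered is decided during the visit. Offer status is therefore a post-randomisation event, and one that the trial hopes to change. If the interventions work, more patients leave the not-offered group in the active arms than in control. The patients who remain then differ in make-up between arms, and stratification covariates (gender and race/ethnicity) do not restore comparability.

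A contrast within that group mixes any effect on follow-up with a change in who is being followed. It could hide a real gain, produce an apparent harm, or produce the hypothesised benefit when there is none.

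A second problem concerns terms. CIDC counts treatment *provided*, while the follow-up standard excludes patients to whom treatment was *offered*. Read literally, a patient who is offered treatment, declines it and receives nothing fails CIDC and has no follow-up standard either.

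**Working it through.** **The plan's own figure (context only).** The article gives no rate or power for the follow-up outcome. Its 170 per arm is for "80% power to detect between-arm (pairwise) differences in the proportion receiving CIDC of 15 percentage points", "under two-sided testing with alpha = 5"%. With pooled variance and no continuity correction, 35% v 50% needs exactly 170 per arm (power 80.2%). The worst case, 42.5% v 57.5%, needs 174 (power 79.2% at 170). The figure reproduces, and only the 15-point effect is carried forward.

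**Inputs from the document (Table 2).** Patients with PHQ-9 ≥ 5: IMCP 99 + 66 + 39 = 204; PSA 103 + 43 + 31 = 177; control 89 + 56 + 33 = 178; total 559. PHQ-9 5 to 9: 99 + 103 + 89 = 291 (52%). PHQ-9 ≥ 10: 559 − 291 = 268 (48%).

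**Assumptions (no rate is given in the document).** The interventions take no offer away and have no effect on follow-up. Let p be the control offer rate and d the rise in offers. There are then three groups: always offered (p), newly offered under active (d) and never offered (1 − p − d). Let f_B and f_N be the rates of timely follow-up, absent an offer, in the newly offered and never offered.

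**Formula.** Among the not-offered:
- control rate = [d·f_B + (1 − p − d)·f_N] / (1 − p)
- active rate = f_N
- false difference, active minus control = −d·(f_B − f_N) / (1 − p)

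**Results with p = 20%.**

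| Rise in offers | f_B v f_N | Control | Active | False difference |
|---|---|---|---|---|
| 15 points | 60% v 30% | (0.09 + 0.195)/0.80 = 35.6% | 30.0% | -5.6 points |
| 15 points | 20% v 40% | (0.03 + 0.26)/0.80 = 36.25% | 40.0% | +3.8 points |
| 7 points | 60% v 30% | (0.042 + 0.219)/0.80 = 32.6% | 30.0% | -2.6 points |
| 7 points | 20% v 40% | (0.014 + 0.292)/0.80 = 38.25% | 40.0% | +1.8 points |

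The 7-point rows take the 15-point effect to be confined to PHQ-9 ≥ 10: 15 × 268/559 = 7.2, about 7 points over Sub-study 1. With 20% v 35% offered, about 0.80 × 178 = 142 control and 0.65 × 204 = 133 IMCP patients would remain.

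**Range.** Take control offers of 10 to 30% and rises of 5 to 15 points. With f_B 50 to 70% against f_N 30%, the false difference runs from -1.1 to -8.6 points. With 20% against 40%, it runs from +1.1 to +4.3. It is zero if d = 0 or f_B = f_N.

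**The all-patient composite (offered, or timely return) in the first row.** Control: 0.20 + 0.15 × 0.60 + 0.65 × 0.30 = 48.5%. Active: 0.35 + 0.65 × 0.30 = 54.5%. The +6.0 points is a randomised contrast, but here it comes wholly from treatment, so the composite cannot be read without its components.

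**The case against.** The strongest objection is that the analysis denominator is inferred. The text defines a standard of care for the not-offered and never says that offered patients are dropped. The Table 1 row names no subset, although the two treatment rows name theirs. Counting offered patients as meeting the standard would also fit, and an analysis plan that is not shown may say so. This stands in part: the restriction is implied, not stated as an analysis set. It does not remove the point, because the only definition written down covers the not-offered and carries a between-arm hypothesis, and the planned regression on arm does nothing about selection.

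The magnitude is also open to challenge, and that challenge stands. Every rate is assumed, and the 15 points are stated for CIDC, not for all of Sub-study 1. Hence the two effect sizes and both signs above.

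Four stronger readings are tempting but unsupported:
- That the not-offered are the complement of CIDC. CIDC covers PHQ-9 ≥ 10 only, and 291 of 559 Sub-study 1 patients lie outside it. The closer complement is the Table 1 treatment outcome for all sub-study participants.
- That patients leave the denominator in the active arms only. They leave in every arm; more leave in the active arms if the interventions work.
- That the bias must make a successful intervention look worse. The sign depends on unknown follow-up rates.
- That the key result is compromised. CIDC is restricted by baseline PHQ-9 alone.

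The stakes are also limited. This is one of several other outcomes, and a Table 1 footnote says that it is not evidence-based.

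**Conclusion.** The concern holds in a bounded form. Followed as written, the definition leads to a comparison of arms within a post-randomisation subset whose make-up differs if the interventions do what the protocol expects. The document cannot tell us how large the bias is or which way it goes. Under the rates assumed above, a few points in either direction is realistic, and no bias is possible. Because the sign is unknown, a difference among the not-offered should not be tested or read as an intervention effect. The definition should be changed, but the defect is confined to a secondary outcome.

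**What to change.** - Define the outcome for all randomised Sub-study 1 patients: antidepressant or referral (offered or provided, one term used throughout), or a return visit within the stated PHQ-9-specific interval.
- Show the components by arm with all randomised patients as denominator. Timely return without an offer falls by construction as offers rise, so it should be read beside the treatment component.
- Report the proportion among the not-offered as descriptive, without a between-arm test.
- Reconcile *provided* and *offered*, and state how patients who are offered treatment and decline are coded. The post-visit questionnaire is described as asking about prescribing, referral and arranged follow-up; check whether declined offers were recorded before choosing the term.
- Leave CIDC and the stated intervals unchanged. Return within the interval regardless of treatment is not proposed, because the document sets no interval for treated patients and that outcome would extend a clinical standard.

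The cost is a redefinition, using the prescribing, referral and follow-up items already collected. The downside is that the composite mixes treatment with follow-up. It should therefore stay secondary and be read with its components, which also respects the decision to keep follow-up out of CIDC.
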